### Aims and Objectives

In the current project, we will collaboratively develop a novel educational program for patients undergoing TKA with orthopedic care teams, consumer advocates, and key health care provider stakeholders, which will focus on providing information that will inform and encourage patients to set realistic expectations of TKA surgical outcomes. The ability of the program to influence the type of expectations patients set prior to surgery will be assessed by comparing patients’ expectations before and after the program and by comparing expectations of those who participate in the program to those who receive “standard clinical care” alone. In addition, the project will determine if education program participation is associated with a higher level of expectation fulfillment, satisfaction with surgical outcomes, and improvement in health literacy. We will apply a number of different methods to define patients’ expectations, using both closed- and open-ended questionnaires to evaluate the scope of responses achieved by each approach.

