#### Activity Expectations

We will use an open-ended question to identify participant expectations relating to their most important activities they want to undertake following TKA [30]. Participants will be asked to identify 3 activities important to them to achieve following the TKA by responding to the following question:

*What activities are you hoping to be able to do after your knee surgery that you cannot do now? (eg this could be an everyday life activity, employment or work activity, social activity, specific movement / motion or exercise etc.)*

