#### Expectation Fulfillment

The level of expectation fulfillment or satisfaction to undertake goals identified will be determined at 6 months after TKA for participants who proceeded with surgery.

For the HSS-TKR items, participants will be asked to indicate the extent of fulfillment of the expectations, identified prior to surgery, using a 5-point Likert scale, ranging from 5 (completely) to 1 (not at all).

The DQO Index will be repeated post TKA, and differences with values obtained prior to TKA will be indicative of the ability to achieve the task.

For activity expectations identified in the pre-TKA assessment, participants will be asked to rate how satisfied they were that each activity could be undertaken using a 7-point Likert scale ranging from 1 (completely dissatisfied) to 7 (completely satisfied).

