#### Satisfaction

At 6 months after the TKA, all participants who underwent surgery will be asked to respond to the following:

*Overall, how would you describe the results of your operation?*

Participants will provide a response on a 5-point Likert scale, ranging from 1 (poor) to 5 (excellent).

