##### Content Analysis of Qualitative Data

The interviews will be conducted by either research team member (KR or LS) during a 30-minute, one-to-one session with the research participant. Each interviewer will review the transcript and validate the content, such that it reflects the PEMAT-AV scores for each video. The content concepts will be identified to reflect the acceptability of the prototype videos or potential changes or edits that need to be considered by the research team. To assist with ensuring the dependability of the data, the interviewers will then review the content analysis undertaken by the other interviewer and again undertake their own validation and identification of content concepts for each transcript. Both interviewers will then meet and compare each one’s content analysis and discuss until a consensus is reached. Coding will be undertaken such that classifiers will be applied to the common concepts identified across all transcripts. The interviewers will then determine if content saturation has been achieved or if additional participants will need to be recruited for the alpha testing.

### Stage 2

Descriptive and inferential statistical analyses will be undertaken to describe the characteristics of the participant cohort and to assess the research hypotheses, respectively. Clinical and demographic characteristics will be described using proportions, measures of central tendency (eg, mean and median), and dispersion (eg, SD, IQR). Inferential statistics will be used to test for differences in, or associations between, outcome measures within and between groups of interest. Methods appropriate to both dependent and independent samples (eg, *t* test, ANOVA, and correlation) will be used, including nonparametric methods for data in violation of normality and variance assumptions (eg, Mann-Whitney *U* and Kruskal-Wallis). The threshold for statistical significance will be set at a *P* value of .05.

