To determine the impact of the health education program to change expectations, the primary outcome measure (HSS-TKR) will be measured and compared between the 2 treatment arms. The within-patient changes of the open-ended measures of patient expectations between T_0_ and T2 will also be compared between the 2 treatment arms to further inform the efficacy of the education platform intervention. We will use data from all participants post surgery to determine the association between expectation fulfillment and overall satisfaction. Activity expectation fulfillment satisfaction and overall procedure satisfaction generate ordinal datasets with associations between the 2 measures undertaken using Spearman rank correlation coefficients.

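### The correlation of activity fulfilment with overall satisfaction pools both randomised arms without adjusting for arm, so a programme effect on both ratings can add to it

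*Protocol article*

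**What the plan says.** The Stage 2 part of Data Analysis first compares the HSS-TKR and the open-ended expectation measures between the arms. It then changes the analysis set: "We will use data from all participants post surgery to determine the association between expectation fulfillment and overall satisfaction". Activity-fulfilment satisfaction and overall satisfaction are described as ordinal, with "associations between the 2 measures undertaken using Spearman rank correlation coefficients". No arm term, stratification or partial correlation is named for this analysis.

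The two variables are defined elsewhere in the article:
- **Activity fulfilment.** Under Activity Expectations, "Participants will be asked to identify 3 activities important to them to achieve following the TKA". Under Expectation Fulfillment, at 6 months, "participants will be asked to rate how satisfied they were that each activity could be undertaken using a 7-point Likert scale".
- **Overall satisfaction.** Under Satisfaction, there is one 5-point rating per patient at 6 months.

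Aims and Objectives says that the project will "determine if education program participation is associated with a higher level of expectation fulfillment, satisfaction with surgical outcomes". The Objective in the abstract likewise has the programme acting on both fulfilment and satisfaction.

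**The concern.** Under the trial's aims, randomised arm may influence both variables being correlated. When two groups differ in the same direction on two variables, pooling them produces a positive correlation even if the variables are unrelated within each group.

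The coefficient would naturally be read as showing that patients whose activity expectations were met are the more satisfied ones. The pooled figure cannot separate that patient-level link from two parallel effects of the programme. The ambiguity grows as the programme becomes more successful, which is when readers would most want to interpret the coefficient.

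**Working it through.** **1. Patients available.** The power calculation uses a 6-point difference, SD 12, alpha .05 and 80% power. The normal approximation gives 2 × (1.960 + 0.842)² × (12/6)² = 62.8, so 63 per arm. The noncentral t gives 64 (power 80.1%; 79.5% at 63), so the stated 64 reproduces. Recruiting 150 and losing 22 leaves 128 = 2 × 64. The article states no figure for the correlation itself.

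**2. Size of r that reaches P = .05.** With N = 128 and a two-sided test (assumed; sidedness is not stated), t is 1.979 on 126 df. The critical value is 1.979 / √(126 + 1.979²) = 0.174.

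**3. Correlation produced by arm alone.** Take 1:1 allocation, arm shifts d1 and d2 in within-arm SD units, and no within-arm association:

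r = (d1·d2/4) / √[(1 + d1²/4)(1 + d2²/4)]

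For equal shifts this is (d²/4)/(1 + d²/4). If either shift is zero, r is zero.

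**4. Approximate rejection rate.** On the Fisher z scale the mean of the test statistic is atanh(r) × √125, compared with ±1.96.

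| Shift on both (SD) | Induced r | Mean of z | Approximate rejection |
|---|---|---|---|
| 0.3 | 0.0225/1.0225 = 0.022 | 0.25 | 5.7% |
| 0.5 | 0.0625/1.0625 = 0.059 | 0.66 | 10.1% |
| 0.8 | 0.16/1.16 = 0.138 | 1.55 | 34% |

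**5. Simulation with ordinal ratings.** Normal latent variables were cut to 7 and 5 levels, with 64 per arm and no association within arm.

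| Shift on both (SD) | Pooled, single 7-level rating | Pooled, mean of three ratings |
|---|---|---|
| 0.3 | 5.0% | 6.6% |
| 0.5 | 8.8% | 11.6% |
| 0.8 | 25.7% | 37.9% |

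The mean of three (correlation 0.5 between a patient's ratings, an assumption) gives higher rates because it varies less than one rating, so the same shift is larger relative to its SD. With a shift of 0.8 SD on only one variable, rejection stays at about 5%.

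**6. After the fix.** With one value per patient and the rank correlation adjusted for arm or stratified by arm, rejection is about 4-6% at every shift examined.

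**The case against.** **Associations within arms are already foreseen.** The abstract's Methods speak of associations within as well as between study arms, and the Stage 2 text says "Inferential statistics will be used to test for differences in, or associations between, outcome measures within and between groups of interest". This is a fair point, but both lines are general. The sentence on this particular association sets the pooled sample and the plain coefficient, and the general lines do not change it. Strengths and Limitations plans to look at covariates of satisfaction but does not name arm.

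**The null scenario is not what the investigators expect.** Potential Impact and Clinical Implementation has the programme improving satisfaction by way of better fulfilment. If so, a within-arm association exists and part of the between-arm component belongs to the same link. This stands as a reason to keep the point modest. It does not remove the point, because the pooled coefficient cannot tell that pathway from two separate effects.

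**Pooling is a legitimate description of the operated cohort, and the analysis is minor.** Both are true. The association is neither the primary outcome nor in the list of secondary outcomes, and the premise that fulfilment matters rests on earlier literature cited in the Background.

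**Two stronger readings are tempting.**
- A reader might infer that the three activity ratings enter as separate, independent rows against one overall rating. The article does not say so. It refers to two measures, and a per-patient summary or one correlation per activity fits equally well. An article may leave that scoring rule to the analysis plan.
- A reader might take 0.5 SD as the design effect for this analysis. The ratio 6/12 was set for the presurgical HSS-TKR score and says nothing about fulfilment or satisfaction at 6 months.

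**Conclusion.** The point holds in a limited form. The article specifies a pooled, unadjusted Spearman coefficient for two variables that the programme is intended to raise, so part of that coefficient may reflect arm.

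Inflation of the 5% test is negligible at shifts of 0.3 SD, small at 0.5 SD and substantial only at about 0.8 SD. It requires shifts on both variables. These figures rest on equal shifts, no within-arm association, 64 per arm and assumed category cut-points. The article supplies none of the shifts, so they illustrate a range and do not predict what this trial will see.

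The randomised comparisons, the primary outcome and the sample size are untouched. Adjusting for arm is worth doing because it removes an ambiguity at almost no cost.

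**What to change.** In the Stage 2 part of Data Analysis, amend the sentence on the fulfilment-satisfaction association to say that:
- each patient contributes one activity value, such as the mean or median of that patient's activity ratings;
- the rank correlation with overall satisfaction is adjusted for or stratified by randomised arm (partial or arm-stratified Spearman);
- the coefficient within each arm is reported beside it with a 95% confidence interval.

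The pooled coefficient may still be shown as a description of the cohort, labelled as unadjusted. The cost is one sentence, a few lines of code and one degree of freedom. No new data or patients are needed.

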### Ethical Considerations

#### Human Subject Ethics Review Approval

This research methodology was peer-reviewed by the Hunter Medical Research Institute-nib grant committee and approved by the School of Medicine and Public Health at the University of Newcastle, New South Wales, Australia, in accordance with the Australian Code for the Responsible Conduct of Research. The study will be conducted according to the National Statement on Ethical Conduct in Human Research (2023). Ethical approval was granted by the University of Newcastle Human Research Ethics Committee (approval ID H-2024‐0312) on January 7, 2025.

#### Informed Consent

All participants taking part in each stage of the study will provide written or electronic consent prior to undertaking any study-related activities. Participant involvement is completely voluntary, and they can choose to withdraw from the study at any time. If they decide to withdraw, they will be asked to notify the research team. The participant will be asked if they consent for any data already collected from them during their study involvement to be used by the research team in their data analysis, or if they prefer that on withdrawal all collected data be destroyed and no longer be accessible for analysis. They will also be asked to provide a reason for their withdrawal, but a response is not mandatory.

#### Privacy and Confidentiality

To enable participants to be contacted, identifiable contact details will be made available to the research team. All data collected and analyzed in both stages of the study will be deidentified. Patient data will be linked between different time points using a unique study code identifier allocated to each participant at the time of study enrollment. Master participant identification decoding records will be maintained and accessible by the chief investigator.

#### Compensation Details

All participants will take part in the study on a voluntary basis with no financial compensation provided.

#### Participant Identification

The deidentified data will be analyzed and presented in publications in scientific journals and at international/national conferences. All data will be presented at a group level, which means that no individual person will be able to be identified in any reports that are generated about the project. Individual participants will not be identifiable in any of the outputs generated from the research project, but individual anonymous responses may be quoted. Nonidentifiable data may be shared with other parties as part of a peer-review process to verify the robustness and integrity of the study or to contribute to further research and public knowledge.

## Results

This study was funded by a grant from the Hunter Medical Research Institute provided by nib insurance in December 2024. We forecast enrolling participants to take part in the alpha testing of the education materials developed in stage 1 of the study in October 2025 to enable finalization of the education program in November 2025. Recruitment to the stage 2 randomized trial designed to evaluate the novel educational materials will take place from December 2025 to September 2026. Final results are expected by April 2027.

## Discussion

### Expected Outcomes

This study responds to the unmet clinical need to address the issue of improving the level of satisfaction experienced by patients following TKA surgery. With the anticipated significant increase in the number of these surgical procedures being performed annually over the next two decades, it is important to consider improving outcomes for a significant number of patients who potentially may experience outcomes that do not meet their expectations following TKA. As the level of satisfaction with surgical outcomes has been shown to be influenced by unmet goals and high expectations of outcomes set prior to surgery, our focus was to enhance the ability for patients to set expectations, which were realistically likely to be met and thereby improve their satisfaction with the outcomes achieved.

We will be engaging in a collaborative consultation process with key stakeholder groups, including consumer advocates and clinical and service provision staff, to support the development of meaningful and accessible education materials that will encourage patients undergoing TKA to set goals that are realistic. The efficacy of the developed educational program will be evaluated in its capacity to impact the expectations of patients undergoing TKA prior to surgery and the capacity to influence postsurgical expectation fulfillment, outcome satisfaction, and level of health literacy. The findings will inform future implementation strategies of the wider application of the educational materials developed.

### Comparison With Prior Work

The approach adopted in this protocol builds upon existing research that has demonstrated the impact of unfulfilled expectations on patient satisfaction with outcomes following TKA. Previous studies have also indicated that Australian patients undergoing TKA set high expectations regarding TKA outcomes, with goals focused on achieving high physical impact pursuits following surgery [29,30]. While several studies have demonstrated the capacity of presurgical education interventions influencing patient expectations regarding TKA outcomes [35,37,75], widespread use of educational materials focusing on setting realistic expectations regarding surgical outcomes has not been adopted. This may, in part, be due to limitations in accurately characterizing patient expectations due to a lack of gold standards to capture this information. There is also a lack of quality educational materials being developed and distributed to patients undergoing TKA [76,77]. To address these issues, we will be using a multimodal approach to characterize patient expectations and expectation fulfillment by applying closed- and open-ended self-report tools to enhance the accuracy of identifying individual patient expectations and goals. We will also be using quantitative and qualitative methods in the alpha testing of the education materials developed with a TKA consumer cohort, which will enhance the quality of the materials being developed, and we will consider these findings to optimize the suitability of the final educational program to be applied. In our study, we will also be determining if our presurgical videos can impact participant health literacy. In a comparison of the influence of a single video presentation regarding osteoarthritis and recovery following total joint replacement in patients with orthopedic conditions compared to that obtained following a preoperative face-to-face consultation with their clinician [78], not only did the video significantly increase patient health literacy, but the level of knowledge improvement was greater than that achieved by those who underwent a preclinical consultation only.

### Potential Impact and Clinical Implementation

If successful, the educational program developed in this study has the potential to impact TKA patient satisfaction with surgical outcomes through improvement of fulfillment of more realistic expectations being set prior to surgery. This will support a more patient-centric classification of surgical “success,” which extends beyond clinical parameters. Improved satisfaction may also reduce usage of health resources postoperatively. The findings will support a broader implementation strategy for a widespread application of the education materials in the clinical setting, which could encompass patients in both the private and public sectors, with the potential to improve patient health literacy and satisfaction with TKA on a large scale. Findings from this study may also influence preoperative processes for other orthopedic surgeries, including total hip replacement and other elective surgical procedures.

### Strengths and Limitations

The strength of the design of the educational materials being developed and tested in this study is the collaborative approach we will be adopting through the involvement of key stakeholders including clinical, research, and consumer groups contributing to the content and format to be used. Alpha testing, involving a cohort of patients who have already undertaken TKA, will also ensure the suitability of the education materials for future patients undergoing TKA. The focus of the material will be specifically targeted at enabling patients to make an informed choice of what expectations they would like to be able to achieve following their TKA and that this expectation is realistic and likely to be achieved. While expectations fulfillment has consistently been associated with post-TKA satisfaction, we acknowledge that other factors may also impact patient satisfaction in our study cohort and, as such, are also measuring a number of clinical, demographic, and psychological patient features in our patient group to evaluate the impact of these covariates on satisfaction with postsurgical outcomes.

We have decided to adopt a mixed methods approach to characterize patient expectations and expectation fulfillment; however, for the purposes of powering our randomized controlled study, we have selected the HSS-TKR as our primary outcome measure. This measure was selected as it has been used to assess the efficacy of education interventions in other studies [35]. While the benefit of this approach enables quantification of expectation level and type to be derived from the provision of a closed-question format, it does limit the type of expectations being characterized to those provided in the survey. For this reason, we have also included a number of open-ended questions which enable the participants to define their own expectations and provide a more individualized approach to characterizing expectations.

Our TKA patient cohort is limited to patients in the private health sector, and we acknowledge that there may be differences in the demographics, clinical, and social features and health literacy of this patient group, compared with those in the public health sector, which may limit the translation of findings to a broader clinical group. In light of this, the findings from this study can be considered a pilot phase, which can inform future implementation of the educational materials developed in this study in a wider range of patients undergoing TKA. Moreover, we anticipate that it will be necessary for external validation of the findings for this study to be verified in a cohort of public patients prior to further implementation approaches being considered. In addition to ensuring equitable access to the educational materials developed, implementation strategies will need to consider the capacity for embedding materials into digital platforms accessible to the target patient population. Differences in cultural settings may also limit the generalizability of findings from this study. Previous studies conducted by our team [30] and findings by others [29] have shown that Australian patients undergoing TKA set high expectations and have goals to achieve high-impact physical activities following surgery, which indeed may not be reflected in other countries.

